## 2.0 STUDY OBJECTIVES

### Primary Aims:

1. Compare the task-shifting (nurse) vs. standard (physician) models on the following quality of care indicators:  
(a) depression treatment uptake, and (b) reduced depression (treatment response). *Hypothesis: Task-shifting model is associated with greater treatment uptake and depression reduction compared to standard model.*
2. Examine the relationship between change in depression and key economic and public health outcomes. *Hypothesis: Reduced depression is associated with better ART adherence, working, and more condom use.*

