## 9.0 STATISTICAL ANALYSES

**9.1 Power analysis for primary aims.** With 10 clusters, this study is powered to detect medium to large effect sizes; nonetheless, the results will be among the first of their kind, hence informative for subsequent analysis and policy. We calculated detectable differences for different intracluster correlation coefficient (ICC) values. Data from developing countries indicate low correlations of health outcome variables within primary care settings (improving power), including .03 for depression in a collaborative care trial in India, and .011 for maternal/perinatal health outcomes in 8 Latin American countries. ICC tends to be higher for process related measures (which would include the focus of Aim 1a): median=.16 for the same 8 country study.

**Aim 1a (treatment uptake):** With 150 patients per site and assuming 30% antidepressant uptake in the standard model and ICC=.16, we will be able to detect an increase of 28% in uptake rates between the task-shifting and standard clinics ( $\alpha = .05$ , 80% power; one sided test). For ICC=.25 the increase is 34%. Given the systematic procedural difference in the two arms, we expect the actual difference may exceed these amounts.

**Aim 1b (depression change):** For measuring change in PHQ-9 in an intention to treat (ITT) analysis using the whole sample, with ICC =.025, s.d. =3.9 (from our current study), and 10% attrition, we'll have power to detect a 1.26 difference on the PHQ-9 ( $\alpha = .05$ , 80% power; 2-sided

test); for ICC=.01 and .05, detectable differences are .92 and 1.71. For analysis of those receiving antidepressants, we estimate 30% (n=45) of the standard arm patients will be treated (a larger share is expected in the task-shifting arm, which will improve power). With ICCs =.01, .025, and .05 (s.d. = 3.0), and 10% attrition, we will be able to detect changes of 1.00, 1.20, and 1.46 in the PHQ-9. These correspond to medium effect sizes (Cohen's *d*) of 0.33, 0.40 and 0.49.

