## 9.2 Statistical Analysis

The analyses must account for clustering of the data, unless the only comparisons are of cluster means or proportions, using clinic as the unit of analysis. For most outcomes we will perform such an analysis first, using standard t-tests or, where the observations per clinic vary, t-tests weighted by cluster-size. However, relative to individual level analysis this approach is limited by low power (low number of clusters); inflexibility in adjusting for baseline individual level covariates; and inability to model direct impacts of patient characteristics and their interactions with treatment. Therefore we will use regression methods on individual level data for most analyses, and the discussion below is largely restricted to these approaches. While such methods can directly model correlations among units in a cluster (random effects or multilevel models) or more simply adjust standard errors for clustering (GEE, robust standard errors), these approaches are not reliable when number of clusters is small: reliably estimating the ICC to adjust standard errors typically requires 20 or more clusters. Hence, we'll use standard regression methods, but rather than attempt to estimate ICC directly, we will explore the sensitivity of significance levels and conclusions to a range of plausible ICCs values for the outcomes.

AIMs 1a: Depression Treatment Uptake: We'll use logistic regression to compare the proportions of depressed patients (according to PHQ-2) receiving depression treatment in task-shifting vs. control arms. We expect that most patients whose PHQ-2 screen is followed up with a formal evaluation and diagnosis of depression will be prescribed antidepressants, so we are not examining this variable separately from treatment uptake; also, it would be difficult to ascertain if the doctor performed a formal evaluation in the standard arm. The treatment uptake outcome will be estimated using covariates to adjust for baseline characteristics such as age, sex, and physical health. We will add interactions of these covariates with study arm to assess which types of patients are likely to be diagnosed and treated in the task-shifting vs. standard models. For example, it is possible that nurses, who are largely female, are more likely to recognize and treat depression in female clients.

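### Section 9.1 sizes uptake with a one-sided .05 test and PHQ-9 change with a two-sided .05 test, without a reason, and the stated 80% power for uptake does not carry over to a two-sided test

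*Protocol*

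**What the plan says.** Protocol section 2.0 states one hypothesis for Primary Aim 1, in the same direction for both outcomes: "Task-shifting model is associated with greater treatment uptake and depression reduction compared to standard model".

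Protocol section 9.1 then sizes the two outcomes separately.

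- **Aim 1a, uptake.** The inputs are given as "With 150 patients per site and assuming 30% antidepressant uptake in the standard model and ICC=.16". The result is "we will be able to detect an increase of 28% in uptake rates between the task-shifting and standard clinics", at alpha .05 with "80% power; one sided test). For ICC=.25 the increase is 34" points.
- **Aim 1b, PHQ-9 change.** The inputs are given "with ICC =.025, s.d. =3.9 (from our current study), and 10% attrition". The result is that "we'll have power to detect a 1.26 difference on the PHQ-9", at alpha .05 with "80% power; 2-sided" testing.

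Protocol section 9.2 plans a clinic-level comparison first, "using standard t-tests or, where the observations per clinic vary, t-tests weighted by cluster-size". It then moves to individual-level models: logistic regression for uptake and a repeated-measures mixed model for PHQ-9. It gives no alpha and no sidedness for either outcome, so section 9.1 is the only place in the document where a test level appears.

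**The concern.** Two outcomes of one primary aim, under one hypothesis, are held to different standards without explanation. There are two ways to carry section 9.1 forward, and each has a cost.

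- **The final tests follow 9.1.** Favourable evidence of the same strength can then pass for uptake and fail for depression. A real uptake advantage of the clinical acumen model, which the protocol also describes as an active task-shifting model, could not be declared at all.
- **The final uptake test is two-sided.** That is how an unqualified t-test or logistic regression is usually read. The detectable differences in 9.1 then belong to a different test, and the trial does not have the stated 80% power for them.

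**Working it through.** **Inputs.** From section 9.1: 150 patients per site, 30% uptake in the standard arm, ICC .16 or .25, alpha .05, 80% power. From section 3.0: 5 clinics per arm. I read the 28% and 34% increases as percentage points.

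**1. What the two levels mean.** One-sided .05 has critical z = 1.645, the same as two-sided .10. Two-sided .05 has critical z = 1.960, which is .025 in the favourable direction. For a test that holds its nominal level, the chance of a false claim in favour of the protocolized model is therefore 5% for uptake and 2.5% for PHQ-9.

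**2. The plan's Aim 1a figures.** Design effect = 1 + 149 × ICC. Effective n per arm = 5 × 150 / design effect.

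- ICC .16: design effect 24.84, effective n 30.2
- ICC .25: design effect 38.25, effective n 19.6

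Solve d = (z_alpha + 0.842) × sqrt{[.30 × .70 + (.30 + d)(.70 − d)] / n}, that is, unpooled variance. The t version uses t quantiles on 8 df (10 clinics − 2) for both terms.

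| Detectable difference, points | ICC .16 | ICC .25 |
|---|---|---|
| Stated in 9.1 (one-sided) | 28 | 34 |
| One-sided, normal | 30.3 | 36.9 |
| Two-sided, normal | 33.9 | 40.8 |
| Two-sided, t on 8 df | 38.0 | 45.4 |

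The stated figures are not reproduced. With pooled variance the one-sided values are 31.3 and 38.7, further away. Using 100 patients per site instead of 150 changes little (30.6 and 37.0 one-sided, unpooled). The unpooled one-sided formula with 6 clinics per arm gives 27.8 and 34.0, but the protocol has 10 clinics, so that explanation is conjecture.

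**3. Power at the stated 28 points, ICC .16.** SE = sqrt{[.21 + .58 × .42] / 30.2} = 0.1226, and .28 / .1226 = 2.284.

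- Normal, one-sided: Phi(2.284 − 1.645) = 74%
- Normal, two-sided: Phi(2.284 − 1.960) = 63%
- Noncentral t on 8 df: 67% one-sided, 52% two-sided

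Pooling the variance under the null gives 72% and 60% in place of 74% and 63%.

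**4. The effect of sidedness alone.** A design with exactly 80% power one-sided has, two-sided, Phi(0.842 + 1.645 − 1.960) = Phi(0.527) = 70%. This does not depend on the ICC or on whether 28 and 34 are right. In points, sidedness accounts for 30.3 to 33.9 (about 3.5 before rounding) at ICC .16 and 36.9 to 40.8 (about 4) at ICC .25. The steps from 28 to 30.3 and from 34 to 36.9 are the separate failure to reproduce.

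**5. Aim 1b for comparison.** With 135 per site after 10% attrition and SD 3.9, d = (z_alpha + 0.842) × 3.9 × sqrt{2 × (1 + 134 × ICC) / (5 × 135)}.

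| PHQ-9 points | ICC .01 | ICC .025 | ICC .05 |
|---|---|---|---|
| Stated in 9.1 | .92 | 1.26 | 1.71 |
| Two-sided, normal | .91 | 1.24 | 1.65 |
| One-sided, normal | .81 | 1.10 | 1.47 |

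The stated values lie close to the two-sided row and well away from the one-sided row. Aim 1b was sized two-sided. For Aim 1a, a two-sided calculation would move the figures further from those stated. Neither label looks like a misprint.

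**The case against.** **Sidedness is only a power input.** Section 9.1 describes sizing. No section defines success, and an analysis plan that is not shown could set the final test. This stands. A reader might infer that an uptake result with two-sided p between .05 and .10 will be declared a success while the same p for PHQ-9 will not. The protocol does not say so. That outcome depends on the final tests using the levels in 9.1, and it arises only when the effect favours the protocolized model.

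**A one-sided test of a directional hypothesis is legitimate, and uptake has its own rationale.** Section 9.1 expects a larger treated share in the task-shifting arm and points to the procedural difference between the arms. That is an expectation about direction and size, not a reason for a weaker level. The depression hypothesis is equally directional and was sized two-sided.

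**Higher uptake under clinical acumen may be unlikely.** A reader might infer that it is likely, on the ground that only the protocolized arm ties prescribing to PHQ-9 and MINI criteria. The text is too mixed for that. Section 6.1 applies confirmed eligibility to prescribers in both arms, section 6.3 supplies the PHQ-9/MINI tools to prescribing providers, and section 11.5 says treated patients will have diagnosed major depression, while section 6.2 leaves evaluation and treatment to judgement. The narrower point stands: both models are active, and a one-sided test rules out declaring a difference in one direction.

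**The ICC matters more than the sidedness.** Going from ICC .16 to .25 moves the one-sided detectable difference by 6.6 points (30.3 to 36.9), against about 3.5 for sidedness, and section 9.2 plans to vary the ICC. True, but varying the ICC does not settle which level applies, and the fall from 80% to 70% holds at any ICC.

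**Conclusion.** The inconsistency is real and is stated in section 9.1 itself: uptake at one-sided .05, PHQ-9 change at two-sided .05, one directional hypothesis, no reason given. What follows from it is conditional. If the final tests use those levels, the false-claim rates in favour of the protocolized model are 5% and 2.5%. If the uptake test is two-sided, a nominal 80% power becomes about 70%.

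Separately, 28 and 34 points are too small for 5 clinics per arm even one-sided. They should not be treated as the result of the one-sided formula, and the whole step from 28 to 34 points at ICC .16 should not be put down to sidedness.

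The recomputed figures assume equal clinic sizes, 30% reference uptake, the ICCs in the protocol and an unadjusted, unpaired comparison. The covariate-adjusted logistic regression could behave somewhat differently.

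**What to change.** - In section 9.1, replace the one-sided test for Aim 1a with two-sided alpha .05, as for Aim 1b.
- In section 9.2, state two-sided alpha .05 for both primary outcomes.
- Restate the Aim 1a detectable differences for 5 clinics per arm: about 34 points (ICC .16) and 41 points (ICC .25) with normal quantiles, or about 38 and 45 with t on 8 df. Say which method was used. The t figures fit the clinic-level t-test that 9.2 performs first.
- If the one-sided level for uptake is kept, justify it explicitly, say why it does not apply to depression, and still correct the 28 and 34 points.

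The change should be fixed before outcomes are compared by arm. It costs wording and a less favourable stated detectable difference for uptake. It needs no extra patients, clinics or data.

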## STUDY OVERVIEW

**DESIGN:** A comparative trial that compares two implementation models for integrating antidepressant treatment into HIV care within 10 health care facilities in Uganda. Using a cluster randomization, 5 clinics are assigned to implement a protocolized model, and 5 others rely on the clinical acumen of trained providers. To evaluate the models, data will be collected from documentation mechanisms integrated into routine care, and from random samples of 100-150 patients enrolled at each site that screen positive for possible depression and are followed for 12 months. A cohort of providers will also be enrolled at each site and followed over 24 months. We will compare the two models on uptake of antidepressant treatment, and change in depression (treatment response), as well as other quality of care outcomes.

**STUDY SITES:** Of the 10 healthcare facilities participating in the study, eight are run by the Ministry of Health and two are private, faith-based, not-for-profit healthcare facilities; two are district hospitals and the others are designated as health centre III or IV facilities by the Uganda Ministry of Health, and are located in the districts of Mpigi, Mityana, Luweero, and Wakiso.

**SAMPLE SIZE:** 10 clusters (clinics), with 100-150 patients at each clinic.

**POPULATION:** Over the course of 12 months at each site, research coordinators (Masters level graduates with social science training) will recruit random samples of 100-150 patients who the triage personnel screen as positive for potential depression (PHQ-2 > 2), who are confirmed to be positive in the research coordinator's own PHQ-2 administration, and who are determined to be medically stable.

**STRATIFICATION:** To ensure the two study arms are balanced on size of clientele (small clinics serve 300-1000 clients, while larger clinics serve 1500-3000 clients), which could influence depression care processes, randomization will be conducted within pairs of clinics that were matched on this variable.

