## 3.0 STUDY DESIGN

INDEPTH-Uganda is a comparative trial that compares two active task-shifting implementation models for integrating antidepressant treatment into HIV care within 10 health care facilities in Uganda. Using a cluster randomization, 5 clinics are assigned to implement a protocolized model, and 5 others rely on the clinical acumen of trained providers. To evaluate the models, data will be collected from documentation mechanisms integrated into routine care, and from random samples of 100-150 patients enrolled at each site that screen positive for possible depression and are followed for 12 months. We will compare the two models on uptake of antidepressant treatment, and change in depression (treatment response), as well as other quality of care outcomes.

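### Aim 1b's stated 80% power for PHQ-9 differences of .92, 1.26 and 1.71 is about 70% in a test valid for 10 clinics (t on 8 df)

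*Protocol*

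**What the plan says.** Protocol section 3.0 sets the design: "Using a cluster randomization, 5 clinics are assigned to implement a protocolized model, and 5 others rely on the clinical acumen of trained providers". The Study Overview gives the size as "10 clusters (clinics), with 100-150 patients at each clinic" and says that clinics were randomized within pairs matched on clientele size.

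Section 9.1 works out the whole-sample (ITT) PHQ-9 comparison "with ICC =.025, s.d. =3.9 (from our current study), and 10% attrition" and concludes that "we'll have power to detect a 1.26 difference on the PHQ-9", with "80% power; 2-sided" testing at alpha .05. It prints .92 at ICC .01 and 1.71 at ICC .05. For patients receiving antidepressants (s.d. 3.0, 30% treated) it prints 1.00, 1.20 and 1.46 at the same three ICCs. Aim 1b names no clinic size of its own. Aim 1a does: "With 150 patients per site and assuming 30% antidepressant uptake in the standard model". No quantile or degrees of freedom are given.

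Section 9.2 plans a clinic-level t-test first for most outcomes and concedes that few clusters make it weak. It then prefers individual-level regression with the ICC assumed over a range, because it regards 10 clinics as too few to estimate the ICC reliably.

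**The concern.** The design effect is one penalty for clustering. A second arises because between-clinic variation has to be judged from only 10 clinics, so the reference distribution is t with few degrees of freedom and not the normal. The printed differences look as though they carry the first penalty only. If so, the power stated for one of the two primary quality-of-care outcomes belongs to a test in which the ICC is known exactly, while section 9.2 says that it cannot be reliably estimated here. The chance of missing a true difference of the printed size would be about 30%, not 20%.

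**Working it through.** **Inputs.** Five clinics per arm (section 3.0). s.d. 3.9, 10% attrition and ICC .01, .025, .05 (section 9.1, Aim 1b). 150 per clinic is carried over from Aim 1a, which is an assumption; less 10%, it leaves m = 135 analysed per clinic.

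**Standard error of the difference.** SE = s.d. × √[2(1 + (m − 1)ICC)/(5m)].

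At ICC .025 the design effect is 1 + 134 × .025 = 4.35, so SE = 3.9 × √(2 × 4.35/675) = 0.443. At ICC .01 and .05 the design effects are 2.34 and 7.70, and the SEs are 0.325 and 0.589.

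**Reproducing the printed figures.** With two-sided normal quantiles the detectable difference is (1.960 + 0.842) × SE = 2.80 × SE. With t on 8 df (10 clinics less 2), the critical value is 2.306 and the noncentral t gives a multiplier of 3.20 for 80% power.

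| ICC | Printed | Normal, 2.80 × SE | t on 8 df, 3.20 × SE | Printed ÷ SE |
|---|---|---|---|---|
| .01 | .92 | .91 | 1.04 | 2.83 |
| .025 | 1.26 | 1.24 | 1.42 | 2.85 |
| .05 | 1.71 | 1.65 | 1.89 | 2.90 |

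The multipliers implied by the printed values (last column) sit near 2.80 and well below 3.20. The fit is loosest at ICC .05.

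**Treated subset.** 30% of 150 is 45 per clinic; less 10% it is 40.5, with s.d. 3.0. Normal quantiles give .99, 1.18 and 1.44 (printed 1.00, 1.20, 1.46); t on 8 df gives 1.13, 1.35 and 1.65. The printed values again follow the normal result.

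**Power at the printed whole-sample differences.** The noncentrality is the last column of the table.

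| ICC | Difference | Normal | t, 8 df |
|---|---|---|---|
| .01 | .92 | 80.9% | 70.0% |
| .025 | 1.26 | 81.2% | 70.4% |
| .05 | 1.71 | 82.7% | 72.0% |

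**Lower end of the clinic-size range.** With 100 enrolled, 90 are analysed. The differences detectable with t on 8 df are 1.14, 1.50 and 1.94, and power at 1.26 (ICC .025) is 65.8%.

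**Keeping the matched pairs.** Five pairs leave 4 df (critical value 2.776). With the same SE, that is with no gain from matching, power at 1.26 is 57.6%.

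**The cited ICC.** Section 9.1 mentions a range of published ICCs, "including .03 for depression in a collaborative care trial in India". At .03, t on 8 df gives 1.52 with 150 per clinic and 1.59 with 100.

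**The case against.** The strongest reply is that the calculation matches the analysis. For Aim 1b section 9.2 specifies an individual-level repeated-measures mixed model and plugs in assumed ICCs instead of estimating one. If the ICC is taken as known, normal quantiles follow, and section 9.1 shows a range of ICCs. The protocol also says that with 10 clusters it can detect only effects of medium size or above, and that the clinic-level approach has low power.

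Part of this stands. Under a known ICC the printed figures are sound arithmetic; that normal quantiles were used is an inference from the reproduction, since the protocol does not say so. The protocol nowhere claims 80% power specifically for the clinic-level test. The restated differences are also not dramatic: at ICC .025, 1.42 against 1.26 is 0.36 against 0.32 of an s.d. (1.42/3.9 and 1.26/3.9).

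It does not rescue the stated power. Section 9.2 puts the clinic-level t-test first for most outcomes and explains why the ICC is not known. Varying the ICC does not replace the degrees-of-freedom penalty, which applies at every ICC in the range. The general remarks about low power put no number on the loss.

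Two stronger readings are tempting. A reader might infer that the base case ought to use ICC .03, making the true figure about 1.5. But .03 is one trial's value and lies inside the printed .01 to .05 range; at the protocol's own .025, the degrees-of-freedom correction alone gives 1.42. A reader might also infer that a null PHQ-9 result would be presented as equivalence. Section 2.0 states a superiority hypothesis, and no section plans an equivalence claim.

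**Conclusion.** The point holds for the printed power figures. In an unmatched test valid for 10 clinics, power at .92, 1.26 and 1.71 is about 70%, 70% and 72%, not 80%. The detectable differences are 1.04, 1.42 and 1.89, which is 10% to 13% above the printed values (1.886/1.71 = 1.10; 1.039/.92 = 1.13).

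This rests on 150 per clinic applying to Aim 1b, equal clinic sizes, the protocol's own s.d., attrition and ICCs, and 8 df. The 8 df is itself a choice: randomization was within pairs, and a paired analysis has 4 df and about 58% power at 1.26 unless matching lowers between-clinic variance. So 70% is not a worst case. The treated-subset restatement is conservative, because it takes 30% treated in both arms while section 9.1 expects a larger share in the task-shifting arm.

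The fault is in the stated power, not in the design.

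**What to change.** In section 9.1, Aim 1b:

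- State the quantile and degrees of freedom, and give the whole-sample detectable differences with t on 8 df at ICC .01, .025 and .05: 1.04, 1.42 and 1.89 with 150 enrolled per clinic, and 1.14, 1.50 and 1.94 with 100.
- Restate the treated-subset values as 1.13, 1.35 and 1.65, which are d = 0.38, 0.45 and 0.55 (each divided by 3.0), and say that they are conservative.
- Optionally add ICC .03 as a further scenario (1.52 with 150 per clinic, 1.59 with 100), not as a new base case.
- Add a sentence on the matched pairs: 4 df and about 58% power at 1.26 if pairs are kept and matching brings no gain.

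The cost is one corrected paragraph with slightly less favourable figures. Design, sample size and conduct stay as they are.
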